## Abstract

**Introduction:**

UK ambulance services have identified a concern with high users of the 999 service and have set up ‘frequent callers’ services, ranging from within-service management to cross-sectoral multidisciplinary case management approaches. There is little evidence about how to address the needs of this patient group.

**Aim:**

To evaluate effectiveness, safety and efficiency of case management approaches to the care of people who frequently call the emergency ambulance service, and gain an understanding of barriers and facilitators to implementation.

**Objectives:**

(1) Develop an understanding of predicted mechanisms of change to underpin evaluation. (2) Describe epidemiology of sustained high users of 999 services. (3) Evaluate case management approaches to the care of people who call the 999 ambulance service frequently in terms of: (i) Further emergency contacts (999, emergency department, emergency admissions to hospital) (ii) Effects on other services (iii) Adverse events (deaths, injuries, serious medical emergencies and police arrests) (iv) Costs of intervention and care (v) Patient experience of care. (4) Identify challenges and opportunities associated with using case management models, including features associated with success, and develop theories about how case management works in this population.

**Methods and analysis:**

We will conduct a multisite mixed-methods evaluation of case management for people who use ambulance services frequently by using anonymised linked routine data outcomes in a ‘natural experiment’ cohort design, in four regional ambulance services. We will conduct interviews and focus groups with service users, commissioners and emergency and non-acute care providers. The planned start and end dates of the study are 1 April 2019 and 1 September 2022, respectively

**Ethics and dissemination:**

The study received approval from the UK Health Research Authority (Confidentiality Advisory Group reference number: 19/CAG/0195; research ethics committee reference number: 19/WA/0216).

We will collate feedback from our Lived Experience Advisory Panel, the Frequent Caller National Network and Research Management Group for targeted dissemination activities.

Strengths and limitations of this studyUse of privacy-protected routinely collected anonymised linked data will provide an efficient, inclusive and holistic picture of service use.Impact likely to be as high as the study is closely aligned to current health and social care policy agenda.Public Patient Involvement throughout the study.Quasi-experimental study design is not as strong as prospective randomised trial.Quantitative health outcomes are based on routine data with no self-reported quality of life outcomes.

## Introduction

### Background

Pressures on emergency ambulance services are growing at an unsustainable rate in Europe and North America.^1–3^ The escalation of emergency calls to the ambulance services presents as a major operational challenge.^4 5^ The volume of emergency calls to ambulance services in England doubled from 4.72 million in 2001/2002 to 9 million in 2014/2015,^1^ and national performance targets were not met for 32 months consecutively.^6^

Emergency ambulance services provide care for those with urgent and life-threatening health conditions. Although most people make few calls to the emergency ambulance service, a small minority of patients make more intensive use.^7^ Unresolved health or social care needs within this group put additional pressure on already stretched emergency ambulance services, which were originally designed to respond to patients with time-critical needs for clinical intervention, rather than to manage non-acute care needs.

Definitions have varied^8 9^ but UK ambulance services agree that people who make five or more calls per month or 12 calls over a 3-month period should be classified as ‘frequent callers’. In London, of a total of 1.7 million calls made during 2014–2015, 1622 people met ‘frequent caller’ criteria and generated 49 534 ambulance attendances, at an estimated cost of £4.4 million to the ambulance service.^1^

Research shows that people who make high use of emergency services also experience higher mortality rates than those with lower use of services.^10^ People who call the emergency ambulance service frequently are often vulnerable,^4 7 11 12^ more likely to be from low socioeconomic group live alone, experience mental health challenges, including self-harming behaviour, live with chronic conditions and have increased chances of falling.^13 14^ Repeated access of services and calling may be because problems are unresolved or patients are not aware of an alternative pathway to access appropriate care.^7 15^

Taking lessons from initiatives in primary care to incentivise the prioritisation of care of frail older patients who are at risk of emergency admission to hospital,^11^ commissioners in the UK now require ambulance services to have management strategies in place for people who call frequently.^10 12^ In some areas, case management approaches are in place, with comprehensive care plans developed for patients who call the emergency ambulance service frequently, through multidisciplinary, cross-sector management groups. Key decision-makers from commissioning, acute, primary, secondary and charitable health and social care providers meet with ambulance service staff to share, stratify risk and manage patients in regular multidisciplinary team meetings.^16^

The introduction of case management has the potential to support a change to safe and equitable out-of-hospital care for this patient group, and to avoid patients being shifted to another part of the emergency care system, wider NHS or social care without their care needs being addressed, but research is needed to evaluate this new approach.

### Research aim

The aim of the study is to evaluate effectiveness, efficiency, safety and patient experience of case management approaches to the care of people who call the emergency ambulance service frequently, and gain an understanding of barriers and facilitators to implementation.

### Research objectives

Develop an understanding of predicted mechanisms of change to underpin the evaluation.Describe epidemiology of people who use the 999 service frequently.Evaluate case management approaches to the care of people who call the 999 ambulance service frequently in terms of:Further emergency contacts (emergency ambulance calls, emergency department (ED) attendance and emergency admissions to hospital). (Note to copywriter: Formatting here and below needs to be amended - as per that on page 2 under Research Objectives)Effects on other health and social care services.Adverse events (deaths, injuries, serious medical emergencies and police arrests)Costs of intervention and subsequent use of health and social carePatient experience of intervention and subsequent use of health and social careIdentify challenges and opportunities associated with using case management models, including features associated with success, and develop theories about how case management works in this population.

## Methods and analysis

### Study design

STRategies to manage Emergency ambulance Telephone Callers with sustained High needs—an Evaluation using linked Data (STRETCHED) is a mixed-methods ‘natural experiment’ evaluation. We will use anonymised linked routine outcomes and qualitative data in four UK ambulance services with one intervention and one control site in each service.

#### Work package 1: logic model

We will develop a logic model in consultation with stakeholders during a face-to-face workshop to underpin the evaluation and inform data collection and finalisation of outcome selection. The logic model will include definition of key components of case management in this setting, predicted mechanisms of change and possible outcomes, positive or otherwise. Stakeholders to be invited to this workshop include clinical and managerial partners working within the ambulance service, EDs, primary care and high-intensity user services from across the UK.

Figure 1 shows a draft logic model, developed from the research literature and specialist knowledge of research team members, to be used as a basis for discussion and development during work package 1 (WP1).

**Figure 1 F1:**
[figure not shown]
Draft logic model. ED, emergency department; GP, General Practitioner.

#### Work package 2: evaluation

We will undertake an evaluation using a natural experiment cohort design in four ambulance services, using quantitative anonymised linked routine data to describe epidemiology and assess effects of the intervention on processes, outcomes, safety and costs of intervention and subsequent health and social care up to 6 months later, with adjustment for covariates, including prior service use. We will also collect qualitative data from focus groups and interviews in each intervention site about the views and experiences of stakeholders (commissioners, emergency and non-acute health and social care providers) regarding acceptability, successes and challenges of case management approaches for this group of patients, and in-depth interviews with a range of service users within the target population.

#### Work package 3: synthesis of quantitative and qualitative findings

We will formally synthesise quantitative and qualitative findings from work package 2 (WP2), informed by the logic model developed in WP1 and in consultation with stakeholders included in the research team.

### Setting

The study will be undertaken in four ambulance services, identified through a survey of practice across the UK, where both case management and traditional ‘within-service’ models are in place in different areas within the service. Emergency ambulance services in the UK which provide emergency are to ‘999’ callers which is free at the point of use. Following mergers in the 1990s, services cover large areas, each serving a population of between 3 million and 9 million people; most cover urban and rural locations and provide a range of emergency responses, including telephone advice, attendance of an emergency vehicle for face-to-face assessment by a paramedic or emergency medical technician, and conveyance to hospital for further care when judged clinically appropriate.

Characteristics of control and intervention site care in the four ambulance service sites included in STRETCHED are summarised in table 1.

**Table 1 T1:** Sites within participating services and key features of control (usual) and intervention (case management) site care

	Control site: usual care	Intervention site: new model of care
Care models: generic description	Aim: to reduce or stop calls made by people making high use of the 999 service Within-service management Letter sent to GP and patient Callers flagged; care management plan developed for use in ambulance call centre to triage patient when call comes in Contact may be made with other services to intervene Police action may be requested	Aim: to address and meet complex patient needs, thereby reducing emergency contacts by people making high use of the 999 service MDT cross-sector case management Usual (within-service) care plus Dedicated frequent caller nurse/prehospital care practitioner funded by CCG/HB MDT meetings attended by ambulance service; partnership approach with other agencies, including district nursing, social workers, police, out of hours providers, mental health professionals, ED, voluntary sector, NHS 111, GPs and occupational therapy to develop and share joint care plans to address patient need

CCG, Clinical Commissioning Group; ED, emergency department; GP, General Practitioner; HB, Health Board; MDT, multidisciplinary team.

### Outcomes

Further emergency contacts:Emergency ambulance calls.ED attendance.Emergency admissions to hospital.Declassification/reclassification as ‘frequent caller’.Effects on other health and social care services.Adverse events, as available:Deaths.Injuries.Serious medical emergencies.Police arrests.Costs of intervention and subsequent use of health and social care.Patient experience of intervention.

### Data collection

We will use a parallel cohort ‘natural experiment’ study design to determine effects on processes and outcomes of care, using anonymised linked data from NHS Digital and the NHS Wales Informatics Service (NWIS). The variation in exposure and outcomes will allow us to carry out analysis to link effects to intervention, that is, causes.^1^ We will include callers meeting the criteria for classification as ‘frequent caller’ by the ambulance service during 2018. We expect to recruit 300 high users per service (n=1200), allowing us to detect a change in rate of further emergency events/death of ±20% with 90% power and 95% confidence (see figure 2). We will finalise data items following completion of the logic model but expect to include (up to 6 months): further calls to emergency ambulance service, ED attendances, emergency admissions and deaths; declassification or reclassification as ‘frequent caller’; costs; and details of demographics, case mix and patterns of calls, for example, ‘out of hours’ (evenings/nights/weekends/holidays). Historical data about prior service use will allow us to adjust analyses for differences between cohorts, strengthening this study design.

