### Data analysis

#### Quantitative analysis

Ambulance services will provide NHS Digital and NWIS with information on recruited patients, to allow matching to anonymised data from multiple sources. We will create a single integrated study database for analysis within the Secure Anonymised Information Linkage (SAIL) Gateway.^17^

We will summarise patient recruitment via a Consolidated Standards of Reporting Trials flowchart,^18^ and will provide descriptive data summaries for patients, by service and by site, for demographics, call patterns and volume. Numbers of events will be dichotomised where contextually useful (for instance, to declassify or reclassify callers), and converted to rates when appropriate.

Our primary analyses will be by treatment allocated, so that patients meeting the criteria for ‘frequent caller’ status in an intervention (case management) site will be included in analysis in that arm of the study whether they were offered or received any intervention. The outcome measure time point will be 6 months from a patient’s first appearance on a monthly update to the ‘frequent callers’ list. This will apply to patients at control sites as well as intervention sites. This time point is appropriate to allow us to detect any effect, as case management is a targeted, time limited intervention designed to work within 6 months.

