We will use multilevel generalised mixed linear models to obtain adjusted comparison of outcomes in patients at intervention sites versus those in patients receiving usual care at control sites. Using linked routine data will allow us to gather retrospective data on service use for callers included in each cohort, strengthening comparisons by enabling adjustment for historical and contemporaneous differences in service use, case mix and demographics. Reflecting an initial focus on comparing (any) case management approach with the service list approach, coding for sites will initially assume that outcomes under usual care are similar across ambulance services, as are outcomes at intervention sites. However, we will use background information on the service interventions, the descriptive summaries and formal testing, based on flexible and nested site coding, to test and modify this assumption, as appropriate—for instance, allowing intervention outcomes to vary systematically from service to service. The precise form of models will reflect the nature of the variable under consideration (logistic models for binary variables, negative binomial models for count variables and linear models for raw and transformed measurement outcomes, including rates); the multilevel element of the model will reflect the geographical clustering of sites within services. The adjusted comparisons will incorporate information on covariates and factors based on demographic and case-mix data. We will formalise these analyses in a Statistical Analysis Plan, using the relevant Swansea Trials Unit Standard Operating Procedure (SOP), which will detail conventions on model fitting (including inclusion and exclusion rules for covariates and factors), management of missing data and the reporting of outcomes.

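### The stated 90% power for a ±20% change shows no allowance for case management varying only between eight sites, and cannot be reproduced from the inputs given

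*Protocol article*

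**What the plan says.** The power statement is one sentence under Data collection. The recruitment figure is "We expect to recruit 300 high users per service (n=1200" in total), and this is described as "allowing us to detect a change in rate of further emergency events/death of ±20% with 90% power and 95% confidence". The sentence refers to Figure 2, which is captioned as a flow diagram and is not reproduced in the text available.

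Study design sets the exposure: the evaluation runs "in four UK ambulance services with one intervention and one control site in each service". Under Quantitative analysis, callers who qualify at an intervention site "will be included in analysis in that arm of the study whether they were offered or received any intervention", so a caller's arm follows from the site alone.

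The same section plans generalised mixed models in which "the multilevel element of the model will reflect the geographical clustering of sites within services". It will at first assume that outcomes are alike across services within each arm, and will then test that assumption and change it where needed. Adjustment for prior service use, case mix and demographics is planned.

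**The concern.** When exposure is fixed by site, the contrast rests on four intervention sites against four control sites. Any difference between sites that is not due to case management enters the treatment comparison directly. Adding callers at the same eight sites does not average it out. A power figure for this design therefore needs some allowance for between-site variation and for the small number of sites. The visible sentence has none, although the planned model recognises clustering by site.

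This sentence is the only justification the article gives for the size of the study. If the 90% depends on favourable inputs that are not stated, a non-significant result could be taken as good evidence against a 20% effect when the study had a much smaller chance of detecting one.

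**Working it through.** **Inputs from the article.** Total 1200 callers, 300 in each of four services; eight sites, four per arm; ±20%; 90% power; 95% confidence, read as two-sided alpha 0.05.

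**Assumed, because not stated.** Equal split (600 per arm, 150 per site); the baseline; the scale of the 20%; the residual intra-site correlation (ICC) within service, or the between-site SD of rates; the degrees of freedom. Power is given for a normal reference (z) and for a noncentral t with 6 df (eight site means) or 3 df (four service pairs).

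**Step 1: can the 90% be reproduced?** Not uniquely. Total N of independent callers for 90% power, by the two-proportion formula:

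| Effect | Total N | 1200 / N | ICC absorbed = (1200/N − 1)/149 |
|---|---|---|---|
| 46% → 36.8% (relative 20%) | 1202 | 1.00 | 0 |
| 50% → 40% | 1038 | 1.16 | 0.001 |
| 60% → 48% | 722 | 1.66 | 0.004 |
| 70% → 56% | 496 | 2.42 | 0.0095 |
| 80% → 64% | 328 | 3.66 | 0.018 |
| 40% v 60% (20 points) | 260 | 4.62 | 0.024 |

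The 1200 matches an individual-level calculation with no slack at a baseline of about 46%. It also fits a smaller base number with a design effect built in. The last column is on z; fewer degrees of freedom leave less room.

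**Step 2: if 1200 is an uninflated number for a relative 20% change.** Design effect = 1 + (150 − 1) × ICC. The noncentrality is (1.960 + 1.282)/√(design effect) = 3.242/√(design effect).

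| ICC | Design effect | Effective N | Power z / 6 df / 3 df |
|---|---|---|---|
| 0 | 1.00 | 1200 | 90 / 77 / 59% |
| 0.001 | 1.15 | 1044 | 86 / 71 / 54% |
| 0.005 | 1.75 | 688 | 69 / 54 / 40% |
| 0.01 | 2.49 | 482 | 54 / 41 / 30% |
| 0.02 | 3.98 | 302 | 37 / 28 / 21% |
| 0.05 | 8.45 | 142 | 20 / 16 / 12% |

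On z, power falls below 80% once the ICC exceeds about 0.0023.

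**Step 3: if the 20% means percentage points.** For 40% v 60%, power (z / 6 df / 3 df) is 99 / 96 / 84% at ICC 0.01, 94 / 84 / 66% at 0.02 and 67 / 53 / 39% at 0.05. Here the stated 90% survives on z up to an ICC of about 0.024.

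**Step 4: the ceiling set by eight sites.** For a rate ratio of 0.8 with unlimited callers, only the between-site SD τ of the log rate remains. The standard error of the log rate ratio is τ√(1/4 + 1/4) = 0.7071τ, and −ln 0.8 = 0.2231.

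- τ = 0.10: 0.2231/0.0707 = 3.156, so power is at most 88 / 75 / 57%.
- τ = 0.15: 0.2231/0.1061 = 2.104, so power is at most 56 / 42 / 31%.

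On z, reaching 90% needs τ below 0.2231/(0.7071 × 3.242) = 0.097, whatever the number of callers. This result does not depend on how 1200 was obtained.

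**The case against.** A reader might infer that the sponsor treated 1200 callers as independent and that the design therefore fails to deliver 90%. The article supports neither statement. It does not say how 1200 was derived, and the number could already include a design effect. The full protocol, which may hold the calculation, is not at hand, nor is the content of Figure 2. Leaving the ICC and dispersion out of a journal article is ordinary condensation.

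Nor does 90% hold only at a baseline near 46%. For a relative reduction, higher baselines give more power. The cohort is defined by very frequent calling, so a baseline well above 50% for any further event is plausible, though none is stated. At 70–80% the design absorbs an ICC of about 0.01–0.02 on z. A percentage-point reading is similarly tolerant.

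The ICC values, the equal site sizes and the 3 or 6 degrees of freedom are assumptions of this check; the article specifies none of them. Adjustment for prior use may shrink residual site variation. A multilevel analysis also does not contradict a power sentence that is silent on clustering.

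All of this stands, and it makes the shortfall conditional. It does not supply the missing support for an unqualified 90%. The figure is asserted as what 1200 callers achieve, the scale of the effect is ambiguous, and the ceiling in Step 4 applies even if 1200 was inflated.

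**Conclusion.** The point holds in conditional form. The article attaches a definite 90% power to a caller count, with no visible allowance for exposure varying only between eight sites. The figure cannot be reproduced, because the baseline, the scale of the 20% and the site-level variation are not given.

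The size depends on those inputs. With 150 callers per site and no slack in the 1200, a relative 20% change has about 86% power at ICC 0.001 and 54% at ICC 0.01 on z, and less with 3 to 6 df. With a high baseline or a percentage-point effect, 90% can survive an ICC of about 0.01–0.02 on z. For a rate ratio of 0.8, a residual between-site SD of about 10% is already enough to put 90% out of reach, however many callers are included. No arithmetic error by the sponsor has been shown; 90% is attainable only under small site variation or other favourable inputs that the article does not state.

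**What to change.** Restate the power under Data collection for an eight-site, service-paired comparison. Give:

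- whether ±20% is relative or in percentage points, and for which outcome;
- the baseline proportion, or the mean and dispersion for a count;
- how 1200 was derived and whether it includes a design effect;
- a range of residual site ICC or between-site CV, estimated where possible from the historical service-use data that the study will hold;
- the small-sample degrees of freedom assumed.

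Report, across that range, the power for a 20% change and the effect detectable with 90% power. The unqualified 90% should not be relied on when a non-significant result is interpreted; the confidence interval from the site-level model should carry that weight.

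The cost is a short recalculation and revised wording. No extra patients are needed. The stated figure is likely to become less favourable.
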